**Methods:**

NEO-MOM is a randomized controlled trial with a three-month behavioral intervention for households involving pairs of 72 stunted children aged 2–5 years old and overweight/obese mothers (SCOWT) in urban Indonesia. The SCOWT pairs were randomly assigned to either an intervention group or to a comparison group that received usual care plus printed educational materials. The intervention consisted of six classroom sessions on nutrition education and home visits performed by trained community health workers using a motivational interviewing approach. The primary outcomes of this study are the prevalence of double burden of malnutrition as measured in SCOWT, child’s height-for-age z-score (HAZ) and maternal body mass index (BMI).

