## Methods/Design

This RCT was a superiority trial consisting of 2-arm parallel groups (an intervention group and a comparison group that received usual care along with printed educational materials). A three-month behavioral intervention was delivered to the two groups made up of households with stunted children aged 2 to 5 years and overweight/obese mother (SCOWT pairs). After an initial screening procedure, the 72 women with stunted children who consented to participate were randomly assigned to either the intervention or comparison group. The study employed parallel assignment with the two groups of participants receiving different interventions during the same time span. The two groups — the enhanced behavior change intervention group (NEO-MOM) and a comparison group receiving printed materials (PRINT) — were each made up of 36 overweight/obese mothers with a stunted child. Baseline data was gathered from participants in their homes at the beginning of the study. Another visit to collect post-intervention data followed the three-month intervention. The adapted CONSORT diagram in Fig. 1 shows progression through the study for individual participants.

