#### Primary hypothesis

The NEO-MOM intervention, consisting of six sessions of behaviorally based nutrition education and home visits, will be more effective in reducing SCOWT prevalence in the intervention group, relative to the comparison group.

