### Target population

The sample was drawn from community health posts *(“posyandu”)* [16] listing more than 50 mothers with children under the age of five. Informed consent was gathered from all participants before undergoing screening to validate their eligibility for participation. The case definition included overweight/obese mothers (BMI > 25) with stunted children (HAZ < -2). A BMI cut-off point of >25 kg/m2 was used to determine maternal overweight and obesity, while child stunting was defined as HAZ < -2, according to the child growth standard from the WHO-Anthro 2005. Repeated anthropometric measurement for both mothers and children are performed by trained research assistance in *posyandu*. A third measurement was initiated when the discrepancy between the first and the second measurement was greater than 1 %. An average of anthropometric measurements was used to determine eligibility. Following screening via anthropometric measurement, those eligible were invited to participate in the study.

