#### Anthropometric data

The secondary outcome measured in this study was maternal overweight/obesity and child stunting or the double burden of malnutrition measured as SCOWT. Data were collected on child’s age, weight and height, as well as maternal weight, height, and waist circumference. Weight was measured in light clothing, without shoes or sandals, on a Camry EB6571 digital scale (Guangdong, China) to 0.01 kg for weight. Height was measured to the nearest 0.1 cm using a stadiometer (SECA 213). Maternal weight and height measurement were used to calculate BMI. Waist circumference was measured horizontally halfway between the lowest rib and the upper prominence of the pelvis using a non-extensible steel tape (MyoTape) placed against the bare abdomen. We measured the change in maternal body mass index (BMI) and child height for age z-score (HAZ) as the secondary health outcome using the 2005 WHO reference standard to assess maternal and child nutritional status. All measurement will be done and recorded twice to ensure the validity. The third measurement will be taken if the difference between the prior two measurement differ by more than 1 %.

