### Statistical analysis plan

We conducted a meditational analysis to examine whether changes in behavioral and psychological factors of the SCT construct (self-efficacy, outcome expectation and goal setting) mediated the association between the intervention and outcomes. Subgroup analysis was used to examine whether the association between the intervention and the outcomes were modified by socioeconomic status (SES), and demographics measured at baseline, such as age, number of children, educational status, employment, and nutritional literacy.

For all variables that are normally distributed or transformed to normality, we analyzed the difference in the outcome between the control and intervention group using a mixed factorial ANOVA. We used the household food insecurity access scale (HFIAS) score as covariates in the analysis. Furthermore, we conducted the ANCOVA test to see the difference in changes of primary and secondary outcomes adjusted for baseline value and the HFIAS score. For nonparametric statistics, we employed the two related-samples Mann Whitney U test and analyzed the data separately for the NEO-MOM group and the PRINT group with Bonferroni correction. All data analyses were performed in IBM SPSS Statistics 22 (Armonk, NY). The statistical significance for all tests was set at an alpha level of 0.05. In the event that after a follow-up of the intervention, the study has high noncompliance or missing outcomes, we planned to conduct an intention-to-treat (ITT) analysis.

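### For SCOWT the planned baseline adjustment is empty, because every pair is SCOWT at entry; baseline child HAZ and maternal BMI should take its place

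*Protocol article*

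**What the plan says.** The protocol article's Statistical analysis plan section first describes a mixed factorial ANOVA for variables that are, or can be made, normal: "For all variables that are normally distributed or transformed to normality, we analyzed the difference in the outcome between the control and intervention group". HFIAS is a covariate there: "We used the household food insecurity access scale (HFIAS) score as covariates in the analysis". It then states a covariate rule for every outcome: "we conducted the ANCOVA test to see the difference in changes of primary and secondary outcomes adjusted for baseline value and the HFIAS score".

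SCOWT falls under that rule whichever rank it holds. The Abstract lists it as primary ("The primary outcomes of this study are the prevalence of double burden of malnutrition as measured in SCOWT"), the primary hypothesis is that the intervention "will be more effective in reducing SCOWT prevalence in the intervention group, relative to the comparison group", and the Anthropometric data section calls it secondary: "The secondary outcome measured in this study was maternal overweight/obesity and child stunting or the double burden of malnutrition measured as SCOWT".

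The Target population section sets entry by the same two cut-offs that define SCOWT: "The case definition included overweight/obese mothers (BMI > 25) with stunted children (HAZ < -2" (closing bracket omitted). Methods/Design says the two arms "were each made up of 36 overweight/obese mothers with a stunted child". Child height and maternal weight and height are measured at baseline and at three months, so HAZ and BMI are available as continuous values at both times. Randomisation uses a sorted list of random numbers, 36 per arm, with no strata.

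**The concern.** Adjusting an outcome for its own baseline is normally sound. Here entry to the trial is defined by having the outcome, so for SCOWT the baseline value is a constant. A constant cannot be told apart from the intercept and explains no variance. Taking change instead of three-month status does not help, because the change is the three-month status minus the same constant.

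The useful baseline information is in the two measurements behind SCOWT. A child just below HAZ -2, or a mother just above BMI 25, can leave SCOWT with a small change. A pair far from both cut-offs is unlikely to leave it in three months. The rule uses these measurements only where HAZ or BMI is itself the outcome, and the design does not balance them. At stake is how precisely the effect in the primary hypothesis is estimated, and how exposed it is to a chance excess of borderline pairs in one arm.

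**Working it through.** **1. The plan's own sample size.** For child height with effect size 0.8, two-sided alpha 0.05 and 90% power:

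n per arm = 2 × (1.960 + 1.282)² / 0.8² = 2 × 10.51 / 0.64 = 32.8, so 33 per arm and 66 in total.

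This matches the article if the SD is 1 cm or 0.8 is a standardised effect. With dropout, 66 × 1.09 = 71.9, so 72 (66 / 0.91 = 72.5 would give 73). These figures concern height. They matter here only because they give 33 evaluable pairs per arm.

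**2. The baseline covariate for SCOWT.** With S = 1 for all 72 pairs, Var(S) = 0. In a model with intercept, arm, S and HFIAS, S is collinear with the intercept and drops out. Arm and HFIAS are left. This step needs no assumption beyond the entry criteria. Screening took place at the health post and baseline collection at home, so a few borderline pairs could be reclassified on remeasurement; S would then be nearly constant rather than exactly so.

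**3. Chance imbalance.** If K of the 72 pairs are borderline, the number in one arm is hypergeometric:

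P(k) = C(K, k) × C(72 − K, 36 − k) / C(72, 36).

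For K = 18 (assumed), a 12-6 split or worse in either direction has probability 17%. For K from 12 to 24, an excess of at least 6 pairs in one arm (6/36 = 17 percentage points) has probability 11% to 21%.

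**4. Size of the benefit.** The documents give no SD of change and no exit rate, so all inputs below are assumptions. Both sets use 33 pairs per arm, and HFIAS was not simulated.

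*Set A.* HAZ from N(-1.6, 1.1) truncated below -2; BMI from N(25, 4.5) truncated above 25; HAZ effect +0.2 (0.80 cm at an assumed 4 cm per z); three BMI effects between 0 and -1.0. Rejection rates in %:

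| SD of change (HAZ / BMI) | Scenario | Firth Wald, arm only | Firth Wald, plus HAZ and BMI | Unadjusted chi-square |
|---|---|---|---|---|
| 0.15 / 0.5 | null | 0.35 | 0.95 | 5.1 |
| 0.15 / 0.5 | three effects | 18, 36, 63 | 24, 45, 70 | 30, 47, 70 |
| 0.25 / 0.8 | null | 1.8 | 2.7 | 5.2 |
| 0.25 / 0.8 | three effects | 13, 24, 44 | 15, 29, 49 | 18, 31, 50 |

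The two Firth columns do not compare like with like, because the arm-only test rejects far less than 5% under the null. With both tests calibrated to 5%, the gain is about 0-8 points. The variance of the risk difference under an effect falls by about 18-23% with the penalised standardised estimator, but by only about 9-13% with plain linear adjustment. Part of the larger figure therefore looks like shrinkage from the penalty. Under the null, the reduction with the penalised estimator is about 5-12%.

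*Set B.* Baseline HAZ on average 0.6-0.9 below its cut-off and BMI 3-5 above; SD of change 0.25-0.4 (HAZ) and 0.8-1.0 (BMI); effects 0.2-0.3 (HAZ) and 0.5-1.0 (BMI). Exit from SCOWT is 9-22% in the comparison arm and 21-49% in the intervention arm. Baseline HAZ and BMI together predict exit in the comparison arm with AUC 0.74-0.78; baseline SCOWT, being constant, has AUC 0.50. Firth Wald power goes from 15-58% to 19-64%, or 4-7 points per scenario. This also comes from the conservative test, so it should not be read as the gain at equal size.

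**The case against.** The strongest objection is that nothing invalid has been shown. Allocation is random, so a comparison without these covariates is unbiased over randomisation, and its confidence interval already allows for chance imbalance. That stands. A reader might infer that the SCOWT result would be biased or its type I error inflated; the documents do not support that. In simulation the mean risk differences with and without adjustment agreed within 0.01.

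A reader might also infer that SCOWT is analysed with no adjustment at all, or that baseline HAZ and BMI largely decide the outcome. The first is wrong because HFIAS stays in the rule. The second is not quantified in the documents; under assumed ranges the prediction is moderate to good.

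The power argument is weak if it rests on the Firth Wald test. An ordinary unadjusted chi-square holds its size and matches or beats the adjusted Firth Wald test in all six effect scenarios of set A. That stands too, and it rules out the Firth Wald test as the main inference.

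It can be said that the rule is an ANCOVA rule following a sentence about normal variables, and that the covariates of a binary model belong to a fuller plan. The missing binary method is indeed not the point here. But the article states the rule for primary and secondary outcomes without exception, and for this one it cannot work. Changing only the model type would leave the same empty covariate.

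Finally, HAZ and BMI are analysed as outcomes with their own baselines. That is useful, but it does not estimate the effect on SCOWT named in the primary hypothesis.

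**Conclusion.** The concern holds in a limited form. That the baseline adjustment is empty for SCOWT follows from the entry criteria alone. The consequence is lost precision and less protection against imbalance in distance to the cut-offs; validity is not affected. The size rests on assumed SDs, effects and exit rates: roughly 10-20% less variance for the risk difference when there is an effect, less under the null, and about 0-8 points of power at equal test size. The gain beyond a model that already contains HFIAS is not known, since HFIAS was not simulated. The benefit is modest, but the data are already collected, so the change is worth making.

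**What to change.** In the Statistical analysis plan section, make an exception for SCOWT. For SCOWT at three months, replace the outcome's own baseline value with baseline child HAZ and baseline maternal BMI, both continuous, and keep HFIAS. Report the covariate-standardised risk difference between NEO-MOM and PRINT with a robust or bootstrap 95% CI, beside the unadjusted proportions in each arm. A penalised fit may be used if events are sparse, but a Firth Wald test should not be the main test, because it is very conservative at this sample size.

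The cost is one or two sentences, with no new data or visits. There are two small drawbacks. Standardisation may need software beyond SPSS 22, which the plan names for all analyses. Two more covariates are also fitted with few events: at the assumed exit rates of 9-22% and 21-49%, 33 pairs per arm give about 3-7 exits in the comparison arm (33 × 0.09 to 33 × 0.22) and 7-16 in the intervention arm (33 × 0.21 to 33 × 0.49).

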#### Secondary hypothesis

We hypothesized that after six sessions of behaviorally based nutrition education (NEO-MOM) accompanied by biweekly home visits, relative to the comparison group, mothers in the intervention group would:Show a greater increase in average maternal fruit and vegetables intake and average child animal protein intake.Show a greater increase in maternal self-efficacy for fruit and vegetable intake, as well as improved child-feeding behavior for protein intake.Show a greater increase in maternal physical activity (average number of steps per day assessed via pedometer).Show larger reductions in maternal sedentary time.

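### The rule for outcomes that stay non-normal names a self-contradictory rank test, run separately in each arm, so on its natural reading it does not compare NEO-MOM with PRINT

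*Protocol article*

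**What the plan says.** The Statistical analysis plan section of the protocol article has two branches.

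- **Parametric branch.** It opens with the condition "For all variables that are normally distributed or transformed to normality" and continues: "we analyzed the difference in the outcome between the control and intervention group using a mixed factorial ANOVA". It then adds, after a linking word, "we conducted the ANCOVA test to see the difference in changes of primary and secondary outcomes adjusted for baseline value and the HFIAS score". Both of these analyses compare the arms.
- **Non-parametric branch.** The whole of it is: "we employed the two related-samples Mann Whitney U test and analyzed the data separately for the NEO-MOM group and the PRINT group", with a Bonferroni correction whose divisor is not given.

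The design and hypotheses are comparative. Methods/Design says "This RCT was a superiority trial consisting of 2-arm parallel groups". The primary hypothesis is that the intervention "will be more effective in reducing SCOWT prevalence in the intervention group, relative to the comparison group", and the secondary hypotheses begin "relative to the comparison group, mothers in the intervention group would". According to the Primary outcome section, outcomes are measured at baseline and after three months.

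**The concern.** Two things look wrong in the non-parametric sentence. First, no related-samples Mann-Whitney U test exists, so the test cannot be identified from its name. Second, with two measurement times, a related-samples test run in one arm at a time is a before-after test within that arm. It gives two p-values, neither of which concerns the difference between NEO-MOM and PRINT.

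What is at stake is how an outcome on this route would be read. If NEO-MOM reaches significance and PRINT does not, it is tempting to report a benefit. That pattern arises often by chance when both arms change by the same moderate amount. A shared change is possible here because both arms receive the same booklets, growth monitoring and access to supplementary feeding (Intervention and Comparison group sections). When the shared change is large, both arms are significant and the rule cannot show whether they differ.

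**Working it through.** **1. The plan's own figure is for a between-arm comparison.** Inputs from Power calculation: effect 0.80, power 90%, two-sided alpha 0.05, minimum total 66, 72 after 9% dropout. The article gives no SD, so an SD of 1 is assumed.

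n per arm = 2 × (1.960 + 1.282)² / 0.80² = 2 × 10.51 / 0.64 = 32.8, rounded up to 33, total 66. This reproduces the stated figure. (A t-based calculation gives 33.8, so 34 per arm.) The trial was therefore sized for a difference between two groups, which the non-parametric rule does not test.

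**2. The test named against the test described.**

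| Element of the sentence | Fits Mann-Whitney U (independent samples) | Fits Wilcoxon signed-rank (related samples) |
|---|---|---|
| Test name | yes | no |
| Related samples | no | yes |
| Run separately in each arm | no | yes |

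Two of the three elements describe a within-arm paired test. If a between-arm test was meant, those two elements are wrong. If a paired test was meant, the name is wrong and the arms are not compared. The sentence needs correction on either reading.

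**3. Chance of NEO-MOM alone being significant when the arms do not differ.** Assumptions, none of them given in the article: 33 per arm analysed, Bonferroni over the two arms (0.05 / 2 = 0.025 each), and the same true change d (in SDs of change) in both arms.

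Let p be the power of a one-sample t-test with n = 33, two-sided alpha 0.025 (critical value 2.352 on 32 df) and non-centrality d√33. The arms are independent, so P(NEO-MOM only) = p(1 − p).

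| d | p | p(1 − p) |
|---|---|---|
| 0 | 0.025 | 2.4% |
| 0.1 | 0.048 | 4.6% |
| 0.2 | 0.128 | 11% |
| 0.3 | 0.279 | 20% |
| 0.4 | 0.487 | 25% |
| 0.5 | 0.698 | 21% |
| 0.6 | 0.857 | 12% |
| 0.8 | 0.985 | 1.5% |

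The ceiling of p(1 − p) is 25%, reached at p = 0.5. Disagreement in either direction is 2p(1 − p), at most 50%, but half of that is PRINT-only significance, which nobody would read as benefit.

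**4. Check with rank tests.** The t-test is only a stand-in, so signed-rank tests were simulated (3,000 runs, n = 33, alpha 0.025 per arm). NEO-MOM alone was significant in the following shares of runs:

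| Common mean change (SD) | Normal changes | Skewed changes |
|---|---|---|
| 0 | 2% | 7% |
| 0.2 | 10% | 4% |
| 0.3 | 19% | 10% |
| 0.4 | 26% | 20% |
| 0.5 | 23% | 25% |
| 0.8 | 2% | 0.3% |

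With 36 per arm the peak was 26.5%. A between-arm Mann-Whitney test on change scores at 0.05 rejected in 4.3% to 5.4% of runs across all scenarios, as it should.

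**5. Sensitivity to the Bonferroni divisor.** With a divisor of 10 (alpha 0.005), the formula in step 3 gives 4%, 10% and 19% at 0.2, 0.3 and 0.4 SD. The rates there are lower, but the peak moves to larger changes (25% at 0.5 SD). A stricter divisor shifts the problem and does not remove it, because neither test estimates the arm difference.

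**The case against.** The strongest reply is that the reach of this sentence is limited, and most of that reply stands.

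- **Not every non-normal outcome is affected.** A reader might infer that any non-normal outcome escapes comparison. Outcomes that transformation makes normal go to the between-arm mixed ANOVA. The ANCOVA sentence also refers to primary and secondary outcomes without repeating the normality condition, so a lenient reader could extend it to the rest. The order of the paragraph (normal variables, then a continuation, then non-parametric statistics) makes the narrower reading the natural one, but the text is not explicit.
- **The primary analysis is probably untouched.** A reader might infer that the powered outcome is compromised. Change in child height is continuous, nothing in the article suggests it would need the fallback, and between-arm analyses are stated for it.
- **Binary SCOWT status is a separate matter.** The section does not assign SCOWT to this rule, so nothing here should be read as a finding on its analysis.
- **The error rates rest on assumptions.** The article gives neither a change distribution nor a divisor, and the rate is small at both ends of the range. Nor does it show a shared shift in the outcomes that plausibly take this route.
- **The wording may be garbled.** The sentence might run together a paired test and an independent-samples test. That is possible, and the within-arm reading is the natural one and not the only one. It does not rescue the sentence, since no between-arm rank test is stated anywhere in the article.

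**Conclusion.** The point holds for outcomes that remain non-normal after transformation. For these, the only analysis named is an impossible test applied within each arm, which on its natural reading cannot answer hypotheses stated relative to the comparison group. This is a rule the article states, not a detail left to a fuller plan.

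The outcomes concerned are not identified. Secondary measures such as step counts, intakes, self-efficacy scores and sitting time are plausible candidates. Under the assumptions shown, a spurious NEO-MOM-only result occurs in roughly 2% to 25% of trials, depending on the common change. That range illustrates the problem and does not predict this trial's results. The case for correction rests on the mismatch between the rule and the design, whatever the exact rate.

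**What to change.** Replace the non-parametric sentence with one between-arm analysis, for example:

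*Outcomes that are not normal after transformation are compared between NEO-MOM and PRINT by rank ANCOVA of the 3-month value on arm, adjusted for baseline value and HFIAS score. The Hodges-Lehmann difference in change with its 95% CI is reported for description. Any Wilcoxon signed-rank tests within an arm are descriptive only and support no conclusion about the intervention.*

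This mirrors the covariates of the parametric ANCOVA and names a single test, so no choice remains after the data are seen. The rank ANCOVA p-value decides. The Hodges-Lehmann interval is unadjusted and may not agree with it exactly, which should be said.

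The cost is one replaced sentence and no new data, since baseline value, 3-month value and HFIAS score are already collected. The section is written in the past tense, so it is unclear whether the change can still be made before analysis. If it cannot, it should be dated and reported as a correction.

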### Randomization and allocation concealment

Randomization of participants was performed using a computer to generate random numbers. After assignment of random numbers to the 72 consenting participants, the list was sorted based on the random number. Thirty-six participants in the upper rank were assigned to the intervention group (NEO-MOM) and the remaining 36 participants were assigned to the comparison group. Because of the nature of the intervention, blinding for both researchers and participants was not possible. The assessor was blind to the intervention condition for baseline and evaluation data collection.

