### Comparison group: usual care plus print educational materials

The comparison group did not receive nutrition education or home visits by a community health worker. Participants in the comparison group received sets of printed educational materials, coupled with benefits from a government food supplementation program. The sets of printed educational materials (booklets) were provided after baseline data measurement for both intervention and comparison group. Printed material was chosen as the medium for source of information due to several considerations: to mimic government strategy for distributing the health messages through the “Kartu Menuju Sehat” (KMS) or a child’s growth monitoring card and because it was deemed unethical not to provide anything for participants knowing they had double burden of malnutrition in the form of SCOWT. Finally, these materials were provided to minimize the threat to internal validity that might occur. By providing the comparison group with the same printed educational materials, we aimed to avoid resentful demoralization of participants in the comparison group. All mothers participating in the study received usual care in the form of monthly growth monitoring of their child’s nutritional status at *posyandu* and access to a supplementary feeding program from Indonesian government. Supplementary feeding program was given for children under 5 years old that consist of foods equivalent with 1000 to 1550 kcal total energy and 25–39 g protein [22].

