### Process evaluation

To provide a sense of the quality of the outcomes to be measured, we conducted several measures of “process evaluation”. First, we monitored adherence to the intervention by making a log of nutrition education sessions including an attendance list filled by our research assistants in the form of biweekly goal-setting sheets completed by mothers at the end of class and following hands-on activity sessions. Through collaboration with the local grocery store, we monitored maternal grocery purchases from the recorded grocery voucher given to mothers each time they attended the class and hands-on session. In addition, a log of daily steps was recorded as a part of the motivational interviewing session with the community health worker during the home visit. Fidelity to the messages and curriculum was monitored by our research assistant that presented at the nutrition education classes, and also from the verbal report and feedback given by the community health workers to our research assistant after the home visit.

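### Intention-to-treat is planned only if non-compliance or missing outcomes prove 'high' after follow-up; 'high' has no threshold and the default analysis set is not named

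*Protocol article*

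**What the plan says.** The only operative statement about who is analysed is the last sentence of the Statistical analysis plan section. It opens with "In the event that after a follow-up of the intervention" and continues that if "the study has high noncompliance or missing outcomes, we planned to conduct an intention-to-treat (ITT) analysis". ITT otherwise appears only in the abbreviation list. No section says that all randomised pairs are analysed in their assigned arm, and none defines a completer, per-protocol or adherer set.

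Four other places bear on this:

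- Methods/Design describes the trial thus: "This RCT was a superiority trial consisting of 2-arm parallel groups".
- Randomization and allocation concealment gives the split ("Thirty-six participants in the upper rank were assigned to the intervention group (NEO-MOM) and the remaining 36 participants were assigned to the comparison group") and states that "blinding for both researchers and participants was not possible". The outcome assessor was blinded.
- Process evaluation reports that "we monitored adherence to the intervention by making a log of nutrition education sessions including an attendance list".
- The comparison-group section states: "The comparison group did not receive nutrition education or home visits by a community health worker".

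**The concern.** In a superiority trial, analysis of everyone as assigned is normally the fixed primary analysis, because it keeps the comparability that randomisation created. Here it is a fallback. Whether it is used depends on a judgement made once attendance and missingness are known, by researchers who know the allocation, against a limit that is not written down. If they judge the problem not to be 'high', the reader cannot tell which pairs enter the comparison of child height.

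Compliance is also not symmetric. NEO-MOM mothers have six classes and six home visits to attend; comparison mothers have neither. Any set defined by session compliance could therefore remove pairs from NEO-MOM only. Mothers who attend may differ from those who do not in motivation and feeding practice. If the children of non-attenders grow less for those reasons, removing them raises the NEO-MOM mean without any treatment effect.

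This is more than detail left to a fuller document. The article states a rule for the analysis set, and a fuller plan could cure it only by saying something different.

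**Working it through.** **The plan's own figures.** The Power calculation section gives an effect of 0.80 cm, 90% power, two-sided alpha 0.05, a minimum of 66, 9% dropout and 72 in total. The SD is not given. With an assumed SD of 1 cm, n per arm = 2 × (1.960 + 1.282)² / 0.8² = 32.8, so 33 per arm and 66 in total. For dropout, 66 × 1.09 = 71.9, so 72 (dividing instead, 66 / 0.91 = 72.5, so 73). The figures reproduce closely and do not depend on the analysis set, so the fix leaves the sample size alone.

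**When the unnamed default applies.** The design allows for 72 − 66 = 6 lost pairs. Loss at the level already planned for is unlikely to be called 'high', so even a trial that runs as expected would probably fall under the default.

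**Size of a one-arm exclusion.** Let a fraction p of NEO-MOM be excluded, with children who gain d cm less than the rest for reasons unrelated to the intervention. If the retained mean is m, the full-arm mean is m − p × d, so exclusion shifts the comparison by p × d. Neither p nor d as used here is in the documents. The 9% is the anticipated dropout, borrowed as an exclusion share; d is assumed to be 0.3 to 1.0 cm.

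| Excluded p | d = 0.3 cm | d = 1.0 cm |
|---|---|---|
| 9% | 0.09 × 0.3 = 0.027 cm (3% of 0.80) | 0.09 × 1.0 = 0.09 cm (11%) |
| 30% | 0.30 × 0.3 = 0.09 cm (11%) | 0.30 × 1.0 = 0.30 cm (38%) |

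The second row applies only if 30% non-compliance were judged not 'high'.

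**If pairs are lost from both arms.** The shift becomes p₁d₁ − p₀d₀, where 1 is NEO-MOM and 0 the comparison arm. It cancels when the two products are equal. A completer analysis with similar losses in both arms would therefore be biased less than the table shows, or not at all.

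**Effect on type I error.** A simulation used 36 per arm, no treatment effect, a two-sided t-test and 8,000 trials per setting. Non-compliers, with outcomes g SD worse, were present in both arms but excluded from NEO-MOM only. The simulation standard error near 5% is √(0.05 × 0.95 / 8000) = 0.24 percentage points.

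| Non-compliers | g = 0.5 SD | g = 1.0 SD |
|---|---|---|
| 9% | 5.2% | 6.2% |
| 20% | 6.6% | 11.5% |
| 30% | 8.6% | 18.4% |
| 40% | 10.9% | 26.1% |

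Analysing everyone as assigned gave 4.4% to 5.3% throughout. At 9%, the inflation is between negligible and about one percentage point.

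**The case against.** The strongest reply is that the text never says non-attenders will be left out. The attendance log belongs to process evaluation, and nothing connects it to membership of the analysis set. The authors may have meant to analyse pairs as assigned throughout and named ITT only as their answer to poor compliance or follow-up. That stands against any claim that the plan adopts a complier analysis. It does not rescue the sentence: an analysis triggered only when a problem is 'high' implies something else when it is not, and the article does not say what.

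Three stronger readings are tempting and are not supported:

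- A reader might infer that the default analysis is known to lack the protection of randomisation. The default is unnamed, so this is an inference and not a stated plan.
- A reader might infer that the trial's result will choose the analysis. The stated trigger is compliance and missingness, not the treatment effect, and the assessor is blinded. What remains is discretion for unblinded researchers with no written limit.
- A reader might take the largest figures above (a shift of 0.30 cm, or type I error of 18% to 26%) as the expected harm. They need 30% to 40% non-compliance, which the rule as written would probably send to ITT.

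The direction is not certain either. Bias toward NEO-MOM assumes that non-attenders' children do worse; if they did better, the bias would run the other way.

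**Conclusion.** The point holds in limited form. ITT is conditional on an undefined threshold applied after follow-up, and the analysis set that applies otherwise is not stated. That much is on the face of the text. That the default differs from ITT is implied. That exclusions would fall on NEO-MOM alone is possible, given who has sessions to attend, but not planned anywhere in the document.

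At the plan's own 9%, the illustrated shift is modest, and it rests on three assumptions: exclusion for non-compliance in one arm only, an exclusion share equal to the anticipated dropout, and a prognostic gap of 0.3 to 1.0 cm. With full compliance and follow-up, the sets coincide and nothing is lost. The case for change rests less on the expected size than on the absence of any written limit, in a rule that decides who enters the main comparison.

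**What to change.** Replace the conditional sentence in the Statistical analysis plan section with:

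*The primary analysis is by intention to treat in all cases: all randomised pairs are analysed in their assigned arm regardless of attendance, using every available 3-month measurement; any adherence-based analysis is supplementary.*

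No new data collection is needed for this. Methods/Design already has a post-intervention data visit that is not tied to class attendance. The sample size does not change. If the data are already in hand, as the article's past tense suggests, pairs can still be analysed by assigned arm. The cost is one sentence, and an estimate that may be somewhat smaller than one in compliers. How missing heights are handled, and which of the listed models is primary, are separate questions that this change does not settle.
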